## Methods

The study is embedded in the larger Physical Activity and Health Equity: Primary Prevention for Healthy Ageing (AEQUIPA) research network that is funded by the Federal Ministry of Education and Research (BMBF) [24]. The AEQUIPA research network is comprised of six subprojects and conducts theory-based and participatory empirical research on different aspects of PA and healthy aging in the northwestern part of Germany [24]. One of the aims of the network is to develop, implement, and evaluate PA interventions for the primary prevention of chronic diseases in adults aged at least 65 years. The first 3-year funding phase was completed in January 2018 [25]. The topic of the research remains the same in the second funding phase (2018-2021); however, in this phase, additional aims are to intensify community participation to reach physically inactive adults, use appropriate technology for PA promotion in the population of older adults, and disseminate and transfer PA interventions as well as results of both funding phases. This study (PROMOTE II) is one of the 6 subprojects of the entire network and builds on knowledge gained during the preceding study (PROMOTE I) [19,25,26].

In the previous study, the research aims were to develop and test 2 individually tailored IT-based interventions for the promotion of a physically active lifestyle in adults aged 65-75 years in a community-based intervention trial [25]. Intervention effects on physical, psychological, and cognitive indicators for healthy aging were examined by comparing 2 intervention groups to a delayed-intervention control group [26]. Results of this trial are reported elsewhere [19,26]. Briefly, the proportion of already active intervention participants at baseline was relatively high. At follow-up, they reported increased social-cognitive predictors for behavior change, but no significant increases in the primary outcome of MVPA when compared with the control group. Also, the dropout rate was higher in the group invited to use PA trackers in addition to the IT-based intervention compared with the IT-only intervention suggesting that individuals with little technological experience might have been randomized to an intervention that they found too difficult to use. In addition, participants in both intervention groups requested printed diaries to track their PA during times that they had limited access to computers. Thus, reactions of the target population during the first funding phase suggested that a proportion of participants prefers a print-based intervention or would appreciate an app for accessing a PA diary on their smartphone or tablet.

### Study Aims

Hence, based on previous findings of the literature and knowledge gained during the preceding trial, this study aimed to adapt and simplify the IT-based intervention of the first funding phase further to improve usability and develop a simple print-based intervention that initially inactive participants with little affinity to technology find easy to interact with; investigate the implementation, feasibility, and use of 2 interventions (IT-based vs print-based) as well as changes in PA among older adults (aged ≥60 years) in a randomized trial with a crossover design over the course of 9 months; examine the role of personal preferences for different delivery modes with regard to intervention effectiveness; and explore associations between changes in PA and possible changes in physical fitness and cognitive capacity in a pooled sample of participants from both phases of funding.

### Selection of Communities for the Study, Participants, and Procedures

We selected 14 community districts in 2 geographically different regions (northwest and northeast) of the city of Bremen, Germany: Burgdamm, Lesum, St. Magnus, Vegesack, Schönebeck, Aumund-Hammersbeck, Rönnebeck, Radio Bremen, Riensberg, Gartenstadt Vahr, Neue Vahr Südwest, Oberneuland, Ellener Feld, and Blockdiek. They were chosen because there are study centers in these districts that can be easily reached by the target group and the project team had already established prior liaisons with stakeholders in these areas of the city who could facilitate community involvement in the implementation of the intervention.

Names and addresses of men and women aged ≥60 years residing in the chosen community districts were drawn from the records of the residents’ registration office. Subsequently, they were invited to participate in the study via mail. Reminders were sent out in case of no response after 2 weeks. The study was also publicized in local newspaper articles and mentioned during talks that targeted older adults by researchers in the team. Individuals made aware of the study through this channel could contact the research team directly to be screened for eligibility. Eligibility for study participation was determined during computer-assisted telephone interviews with trained study nurses based on the inclusion and exclusion criteria.

### Inclusion and Exclusion Criteria

Men and women were eligible for study participation if they were aged ≥60 years (there was no upper age limit), lived independently (ie, in own apartment or room without assisted living or regular home nursing), and provided informed consent to participate in the study. Additional inclusion criteria were basic knowledge of German, the ability to walk without a walking aid and participate in study assessments and weekly group meetings without external assistance, and no planned long absence (ie, for more than 2 weeks). Another precondition was the availability of a device with internet access in the household, regular access to the device, and the ability to use it.

Individuals were excluded from the study if they reported that they had already been regularly physically active for more than 1 year and had reached the intervention target (ie, the recommended 150 minutes of moderate-intensity endurance training per week). They were also excluded if they reported having participated in the preceding study (PROMOTE I), had planned a vacation lasting longer than 2 weeks during the intervention period, had been medically prohibited to be physically active, displayed severe visual or cognitive impairment (Mini-Mental-State Examination Score ≤14) or other impairments (eg, due to a stroke, transient ischemic attack, brain surgery, or neurological diseases, such as Alzheimer’s disease, multiple sclerosis, or Parkinson’s disease), had an implanted device (eg, pacemaker, implanted hearing aid), or experienced occasional syncope. Additional exclusion criteria were a lack of medical clearance because of fractures or surgeries in the past 6 months that could potentially constrain study participation; report of severe diseases of the cardiovascular system (eg, cardiac arrhythmia, heart failure, or nonmedicated hypertension) or respiratory system (eg, COPD, severe asthma); or severe limitations due to arthritis or osteoarthritis in the legs or severe osteoporosis or acute injuries of the spine. Individuals with diabetes diagnosed less than 6 months prior and without medical clearance were also excluded from the study.

### Study Design

After determination of eligibility, study participants were randomized to either an IT-based intervention or a print-based intervention (see Figure 1). In the first group, 30% were randomly selected to receive a PA tracker in addition to access to the website. Weekly time slots were randomly assigned to both intervention groups. Then, we had participants choose appointments according to their personal time constraints without knowing which intervention group they were assigned to. All intervention groups were offered weekly group sessions, and participants were encouraged to attend each of them. Two weeks before the intervention started, participants in all groups attended an introductory event where they were informed about the study background and procedures. On this day, data collection also started, and participants received the activity tracker and questionnaires for the first time (T0). They were also briefed about their randomization to one of the intervention groups and the existence of the other groups. Therefore, they were not blinded. Participants were given the choice to remain in their intervention group or to cross over to the other group after 3 months (and a 10-week intervention period). With that, a crossover design with the following possible combinations was generated: IT-IT, print-print (matched), or IT-print and print-IT. Preferences regarding the intervention material assessed retrospectively at the 9-month follow-up will be taken into account when analyzing intervention effects later in the study. Research staff members conducting the study were not blinded, and the statistician will not be blinded when analyzing the data.

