### Analytic Strategy

Effects of time and group (main outcomes: subjective and objective measures of PA) will be examined in multivariate analyses. In addition, covariates, such as gender, age, and preferences regarding intervention material, and individual contextual factors (eg, living or social environment) will be taken into account. Furthermore, we will analyze how the intervention enables study participants to change their behavior by running mediation analyses. The estimated target sample size of 390 participants for this study is based on the results of 2 recently published studies on PA in adults [27,28] that reported a mean 111 weekly minutes (SD 116.8 weekly minutes) of MVPA and an intervention effect of an increase in MVPA of 77 minutes per week. However, in a conservative (or realistic) approach, we assumed that the mean increase in MVPA in our study will reach only 40 minutes/week. To detect such a difference between the intervention and control groups with a power of 80% at an alpha of .05 (two-sided), a net sample size of 150 subjects for each group is required. Assuming a loss to follow-up from T0 to T1 of 20-25% (ie, ca. 23%), it is necessary to initially recruit 390 study participants (ie, 195 per group at baseline). Assuming another 20% loss to follow-up from T1 to T2, we expect that approximately 240 individuals at T2 will self-select to one of the 4 groups: IT-IT, print-print, IT-print, or print-IT. Should participants self-select equally into each group (n=60), we will still be able to detect the mean difference of 77 minutes/week [28] between each group, by means of an appropriate post hoc test that is adjusted for multiple comparisons.

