Anthropometric information, as self-reported in the questionnaire, included height in cm (only T0) and weight in kg (all time points). Sociodemographic information was assessed at baseline only, using items of the German Health Interview and Examination Survey for Adults [63] for date and country of birth, gender, native language, family and relationship status, living situation, education, employment status, and monthly net household income. Employment was assessed using one item of a questionnaire for assessing seniors’ demographic and sociostructural data in Germany [64]. In addition, the self-administered questionnaire at T1 and T2 includes self-generated items regarding adherence to the PA recommendations (weekly minutes of endurance, balance, and flexibility training and weekly units of muscle strength training per muscle group) and attendance of the offered group sessions. Furthermore, use and satisfaction with the intervention material and content are assessed with the following self-generated items: frequency of general use; use of different intervention components reporting using a 5-point Likert scale from “never” to “daily”; perceived helpfulness of intervention components, intervention content, and structure of weekly meetings rated on a 5-point Likert scale ranging from “not helpful at all” to “very helpful”; potential knowledge gained and perceived benefits of PA using “yes” and “no” response options; and whether participants would recommend the intervention to family and friends, answered using open-ended questions. Data on the reasons for dropping out of the study and the reasons for crossing over or not crossing over to the respective other intervention group were also collected.

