**Figure 2 figure2:**
[figure not shown]
Weekly overview of physical activity performed, as provided to participants in the IT-based intervention group.

Paralleling the 10-week IT-based and print-based interventions, weekly group sessions with up to 25 participants per group were offered separately to both intervention groups. Trained student assistants led these sessions in which participants performed endurance, strength, balance, and flexibility exercises in groups or went for walks in the communities. Each session was 90 minutes long and designed to include 60 minutes of exercise, 10 minutes of answering questions, and 20 minutes of discussion of topics surrounding healthy aging that changed every week (eg, social support, relaxation, pain management). During their first weekly group meeting, participants received the necessary equipment (printed material or information to access the website and/or a Fitbit) and a comprehensive introduction on how to use the equipment and materials. After the first follow-up, interventions continued for another 6 months. After the initial 10 weeks of the interventions, the weekly group meetings were replaced with monthly events held over the course of the following 6 months. During these events, participants of all intervention groups were offered workshops and lectures on lifestyle-related topics, such as healthy nutrition in older age, overcoming loneliness, and strategies for developing healthy habits.

We will develop a toolbox during this project that will include both IT-based and print-based interventions and all related intervention materials that can be used later for long-term implementation and dissemination via different stakeholder groups (for further detail, please see the Discussion).

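### The protocol describes two allocation steps, of persons and of time slots, without saying which one fixed the arm; if it was the slot, an individual-level analysis overstates precision

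*Protocol article*

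**What the plan says.** The Study Design section of the protocol article gives three statements in this order:

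1. "After determination of eligibility, study participants were randomized to either an IT-based intervention or a print-based intervention".
2. "Weekly time slots were randomly assigned to both intervention groups".
3. "Then, we had participants choose appointments according to their personal time constraints without knowing which intervention group they were assigned to".

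The same section says that participants learned their arm at the introductory event, two weeks before the intervention began, where T0 data collection also started: "They were also briefed about their randomization to one of the intervention groups and the existence of the other groups". The Interventions section ties session to arm: "weekly group sessions with up to 25 participants per group were offered separately to both intervention groups".

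On the analysis, the Analytic Strategy section says that "covariates, such as gender, age, and preferences regarding intervention material, and individual contextual factors (eg, living or social environment) will be taken into account". Slot and session group are not named. The sample size there compares two groups of independent individuals, and its loss allowance runs from T0 to T1. The Measures section lists the sociodemographic items collected at baseline, among them "living situation, education, employment status, and monthly net household income".

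**The concern.** Because sessions were separate by arm, a participant's slot and arm go together. The text leaves two sequences open, and they are different designs.

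- **Slot fixes arm.** Slots were drawn to arms and the participant's blind choice of slot decided the arm. Concealment holds, but the randomised unit is the slot. With few slots, chance can place a cluster of people with similar timetables mostly in one arm. Standard errors computed as if each person had been randomised are then too small.
- **Person first.** The arm was drawn for the person, who then chose among that arm's slots only. Randomisation is individual. However, someone whom none of those slots suits has been randomised and may drop out before any data are taken.

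The IT-versus-print comparison is the trial's main aim. What it can support depends on which sequence was used.

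**Working it through.** **The plan's own sample size.** The inputs come from the Analytic Strategy section: difference 40 min/week, SD 116.8, two-sided alpha 0.05, power 80%.

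n per arm = 2 × (1.96 + 0.842)² × 116.8² / 40² = 134 after rounding up.

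The plan states 150, which is on the safe side: power at 150 per arm is 84.3%. The loss step reproduces: 150 / (1 − 0.23) = 195 per arm, 390 in total. The point does not depend on the gap between 134 and 150. What matters is that the calculation treats individuals as independent.

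**Number of slots (assumption).** The documents give only the maximum of 25 per group. 390 / 25 = 15.6, so about 16 slots, or 8 per arm. Smaller sessions would mean more slots.

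**Precision if the slot is the unit.** Design effect DE = 1 + (m − 1) × ICC, with m = 150 / 8 = 18.75 analysed per slot. The ICC is not given, so a range is shown. Intervals widen by √DE. The type I error of an analysis ignoring slots is 2 × [1 − Φ(1.96 / √DE)].

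| ICC (assumed) | DE | Interval width vs independent | Type I error if ignored | Power at 150 per arm, normal | Power, t with 14 df | n per arm for 80% (normal) |
|---|---|---|---|---|---|---|
| 0 | 1.00 | 1.00 | 5.0% | 84% | 79% | 134 |
| 0.01 | 1.18 | 1.09 | 7.1% | 78% | 72% | 158 |
| 0.02 | 1.36 | 1.16 | 9.2% | 72% | 66% | 182 |
| 0.05 | 1.89 | 1.37 | 15.4% | 58% | 52% | 253 |

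With m = 25 throughout, DE is 1.24, 1.48 and 2.20, and power at 150 per arm (normal) is 76%, 68% and 52%. With m = 15 it is 79%, 75% and 62%.

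**Illustration of uneven slots.** Suppose 4 of 16 slots are of a kind that suits one type of schedule, and 8 slots go to each arm. There are C(16,8) = 12870 equally likely draws.

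- 2:2 split: C(4,2) × C(12,6) = 6 × 924 = 5544, or 43%
- 3:1 split: 2 × C(4,3) × C(12,5) = 2 × 4 × 792 = 6336, or 49%
- 4:0 split: 2 × C(12,4) = 2 × 495 = 990, or 8%

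The result moves with the assumed number of special slots. With 2, an even split has probability 2 × C(14,7) / 12870 = 6864 / 12870 = 53%. With 6, it is C(6,3) × C(10,5) / 12870 = 5040 / 12870 = 39%. These figures count slots. They do not give an imbalance in persons or a shift in MVPA.

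**If persons were randomised first.** The section describes slot choice before the introductory event, where T0 begins. If that was also the order in time, a person lost because no slot fitted has no T0 data. The 23% allowance starts at T0 and so excludes that person. No size can be given, because the documents report no such losses.

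**The case against.** The strongest reply is that the trial was individually randomised and says so. The Abstract, the Introduction and the opening of Study Design all have participants being randomised. The slot sentence speaks of the group to which people were already assigned, which reads naturally as arm first and slot second. Figure 1 is not available here and may show the order. This stands as far as it goes: slot-based allocation is a plausible reading, not an established fact. It does not close the matter, because no sentence restricts the choice to slots of the person's own arm.

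A reader might go further and infer that the arms differ systematically because timetables decided who joined which. The documents do not support that. Slots were assigned at random and chosen without knowledge of arm, so neither arm is favoured in expectation. What remains is chance imbalance over few units, which belongs to the between-slot variation in the table. By the same reasoning, losses for want of a suitable slot are equal by arm in expectation under the other reading; the concern is that they would go uncounted.

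A reader might also take employment to be the main driver of slot choice. The protocol mentions only personal time constraints. Employment is worth including because it is a baseline item plausibly related to schedule, not because the documents show that it decides slots.

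Finally, the covariate list is open ("covariates, such as gender, age, and preferences regarding intervention material" is introduced as examples), T0 activity already enters a change outcome, and the exact covariate set may sit in an analysis plan that is not shown. All of that is fair, so the absence of employment or region from the list is not itself an error. The unit of allocation is different: the article sets out that sequence itself and leaves it ambiguous.

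**Conclusion.** The concern holds as an ambiguity with a real consequence. The protocol does not say whether the arm was fixed by randomising the person or by the slot the person chose.

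If it was the slot, an individual-level analysis is too precise. With about 16 slots and an ICC of 0.01 to 0.05, the type I error would be roughly 7% to 15%. Power at 150 per arm would be about 72% to 52% once the few slots are allowed for (t with 14 df), against the planned 80%. The slot count and ICC are assumptions. The 43%/49%/8% split only illustrates how uneven a few slots can fall; whether an uneven split is the likelier outcome depends on the assumed number of special slots.

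If persons came first, individual randomisation stands. The remaining issue is an uncounted loss between randomisation and T0, of unknown size.

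The text does not establish that the trial was slot-randomised, nor that the arms are systematically different.

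**What to change.** Data collection has ended, so the remedy lies in reporting and analysis.

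1. State from the trial records which step determined the arm, and how many slots each arm had.
2. If it was the slot, describe the trial as randomised by time slot. Account for slot or session group in the IT-versus-print analysis, for example by a random effect or cluster-robust standard errors with a small-sample correction. Person-level covariates alone would leave the standard errors uncorrected.
3. If persons were randomised first, count by arm those lost because no slot fitted, and keep them in the randomised denominator.
4. Under either reading, adjust the primary model for T0 MVPA, region (northwest or northeast) and T0 employment status, and show their balance by arm. Activity and employment are collected at T0, and region should be known because recruitment was by district.

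The cost is a sentence or two of design wording, a count from the records and a few covariates already in hand. If the slot was the unit, intervals become somewhat wider and the design carries a less favourable label.

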### Measures

The primary outcome is change in PA, which is assessed at baseline, 3 months, and 9 months using triaxial accelerometers worn at the right hip during the day over the course of 7 days and a self-administered questionnaire. Participants received the self-administered questionnaire and accelerometer at their introductory event at baseline (T0), after 3 months (T1) at their tenth group meeting, and after 9 months (T2) at their last monthly meeting. Further, due to cost issues, a random subsample of 114 participants (equally distributed across the intervention groups) underwent additional anthropometric, physical fitness, and cognitive tests to assess secondary outcomes at all 3 time points. Physical fitness was assessed using gait speed via a 4-meter walk test [29], handgrip strength using a dynamometer [30], and cardiovascular fitness using the 2-minute step test [31]. Additionally, participants’ weight was assessed using a scale. Attention and inhibition were assessed using a cognitive test (Simon task) [32].

Data from the objective measures of physical fitness and cognitive performance (Mini Mental State Examination and executive function test) will be preprocessed using customized MATLAB routines and analyzed using multivariate generalized linear models. Data for physical fitness and cognitive performance assessed at baseline and after the 10-week intervention during the first funding phase and in the subsample of participants during the second funding phase will be pooled to increase power for data analysis and to meet sample heterogeneity. Further, the larger sample size will enable us to conduct subgroup analyses with respect to motivational stage, activity behavior, and social engagement.

All participants underwent a short version of the Mini Mental State Examination during their first weekly group meeting [33]. Motivational stages to engage in recommended PA (endurance, strength, flexibility, and balance training), social-cognitive predictors for behavior change, and psychosocial factors (eg, quality of life, depression) were assessed in the self-administered questionnaire (for further detail on the instruments included in the questionnaire, see Table 1).

**Table 1 table1:** Measures assessed in the self-administered study questionnaire.

Outcome measure		Instrument/scale	Time of assessment

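### The T0 accelerometer week, and probably the T0 questionnaire, follow disclosure of the arm, so change from T0 can absorb a reaction to allocation

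*Protocol article*

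**What the plan says.** The order of events is stated in three sections of the protocol article.

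- **Before the event (Study Design).** Participants chose their time slots "without knowing which intervention group they were assigned to".
- **At the event (Study Design).** "Two weeks before the intervention started, participants in all groups attended an introductory event". Of that day the article says "On this day, data collection also started, and participants received the activity tracker and questionnaires for the first time (T0"), then "They were also briefed about their randomization to one of the intervention groups and the existence of the other groups", and concludes "Therefore, they were not blinded".
- **Instruments (Measures).** "Participants received the self-administered questionnaire and accelerometer at their introductory event at baseline (T0"). The accelerometer is worn for 7 days. The device called an activity tracker in Study Design is therefore the study accelerometer, not the Fitbit.
- **Materials (Interventions, after Figure 2).** "During their first weekly group meeting, participants received the necessary equipment". The diary, website access and Fitbit thus came after the event.
- **Outcome (Measures).** "The primary outcome is change in PA", assessed at T0, T1 and T2.

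The Discussion explains that preference was recalled later, rather than asked at baseline, because the authors expected people not given their preferred arm to be disappointed and perhaps to drop out. Its limitations cover the missing control group, hard recruitment and recall bias. They do not mention that T0 follows disclosure.

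**The concern.** A baseline used to measure change should not be open to influence by knowledge of the arm. Here it is, and the authors themselves expected a reaction to allocation. Two distortions are possible.

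- **A reaction that differs by arm.** It enters the between-arm contrast of change in full, with reversed sign. If one arm starts moving early, its later gain looks smaller. If one arm is discouraged, its later gain looks larger.
- **A reaction common to both arms.** It cancels between arms but not within them. It would distort the increase over baseline that the Results section expects at 3 months. It would also distort the comparison of that increase with the earlier study's control group and the classification by a 25% rise from baseline.

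The T0 values of intention, self-efficacy and technology commitment probably share the problem, which bears on the planned mediation analyses.

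**Working it through.** **1. Sequence.** Time slots chosen with the arm unknown → introductory event (accelerometer and questionnaire handed out; arm disclosed) → 7-day wear → first weekly meeting (materials issued). Wear lasts 7 days from a device received at the event, so essentially the whole T0 accelerometer record follows disclosure. For the questionnaire this is probable only: it is self-administered and handed out at the event, but the article does not say whether any of it was filled in before the briefing.

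**2. Inputs from Analytic Strategy.** SD of MVPA 116.8 min/week; target difference 40 min/week; 150 per arm at T1; 195 per arm at T0. The attrition step reproduces: 150 / (1 − 0.23) = 194.8, so 195 per arm and 390 in total. The article gives no figure for a reaction to disclosure.

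**3. Assumptions (not in the documents).** Disclosure raises T0 MVPA by s min/week more in one arm than in the other, with s from 5 to 20. The T0–T1 correlation is r = 0.5, with equal variances at T0 and T1.

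**4. Bias of each contrast.**

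| Contrast | Bias | s = 5 | s = 10 | s = 20 |
|---|---|---|---|---|
| Change score | −s | −5 | −10 | −20 |
| Baseline-adjusted | −r × s | −2.5 | −5 | −10 |
| T1 values only | 0 | 0 | 0 | 0 |

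Against the 40 min/week target, the change-score bias is 5/40 = 12.5% to 20/40 = 50%.

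**5. Effect on power of a change score.** At r = 0.5 the SD of change is 116.8 × √(2 × (1 − 0.5)) = 116.8. With 150 per arm and a true difference of 40, two-sided alpha 0.05, power is 84% at s = 0, 74% at s = 5, 60% at s = 10 and 32% at s = 20 when the shift is adverse. A shift the other way would inflate the difference instead.

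**6. Price of dropping T0.**
- T1 only: SE = 116.8 × √(2/150) = 13.5 min/week.
- Baseline-adjusted: 13.5 × √(1 − 0.5²) = 11.7 min/week.

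Root mean squared errors are equal when 11.7² + (0.5 s)² = 13.5². With unrounded values this is 136.4 + 0.25 s² = 181.9, so s ≈ 13.5 min/week. Below that the baseline-adjusted contrast is the better estimator; above it T1-only is.

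**7. Can a T0 comparison by arm detect the shift?** SE = 116.8 × √(2/195) = 11.8 min/week. Power is about 7% for s = 5 and 39% for s = 20.

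**The case against.** **The size is assumed and close to a worst case. This stands.** The larger figures need a net shift in one arm and an unadjusted change score. The article does not commit to a change score; it speaks of time and group effects in multivariate analyses with covariates. Both arms are active, with the same recommendations, a diary and weekly sessions, and everyone had to have and be able to use an internet device. Much of any reaction could be common and cancel between arms. Disappointment can occur in either arm, so only the net imbalance counts. Anticipation of the Fitbit concerns 30% of one arm: to move that arm's mean by 5 to 20 min/week, those participants would have to shift by 5/0.3 = 17 to 20/0.3 = 67 min/week.

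**The data are already collected. This stands.** Collection ended on January 31, 2020, analysis began in February 2020, and the statistician is not blinded. Reordering helps only further use of the design, and no new analysis can be called prespecified.

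**A T0 comparison by arm settles nothing. This stands.** Its power is low, a difference could be chance imbalance, and it cannot see a common shift.

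**T1-only is not generally superior. This stands.** It is less precise, wins only for shifts above about 13.5 min/week, and does nothing for the within-arm increase.

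**Later disclosure has a cost. This stands.** It may move some disappointment-driven dropout to after T0. The article gives no reason for the timing it chose; that nothing required disclosure at the event is an inference from when materials were issued.

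**The sequence is openly reported. This stands only in part.** Study Design describes it and says participants were unblinded, but nowhere is the consequence for change from T0 drawn.

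**Conclusion.** The point holds as a risk of bias built into the stated sequence. It is certain for T0 accelerometry and probable for the T0 questionnaire.

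A reader might infer more, and the documents do not support it:
- They do not show that T0 values moved, in which direction, or by how much. The 5 to 20 min/week range, and so the 12.5% to 50% of target, is illustration under assumptions.
- They do not establish that all T0 self-report was given with the arm known.
- They do not support discarding T0. At r = 0.5, adjusting for it gives the lower root mean squared error for shifts up to about 13.5 min/week.
- Randomisation precedes T0 in any case. Later disclosure would make T0 a pre-disclosure measure, not a pre-allocation one.

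What remains is an inexpensive improvement to the procedure, one sensitivity analysis and one limitation to state. The T1 comparison by randomised arm can still be protected. Within-arm conclusions from T0 cannot, and need the caveat.

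**What to change.** **For any further use of the design.** Reveal the arm only after the T0 accelerometer week and questionnaire are complete, for example at the first weekly meeting, when materials are issued anyway. The cost is moving one briefing, with the possibility that some dropout from disappointment then falls after T0.

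**For the data already collected.**
1. Make a baseline-adjusted contrast of T1 by randomised arm the main between-arm analysis, rather than a raw change score. It carries only about r times any differential shift.
2. Add a contrast of T1 values alone by randomised arm as a sensitivity analysis, labelled as added after data collection. The cost is one extra model and some precision: SE about 13.5 instead of 11.7 min/week at 150 per arm, assuming r = 0.5.
3. List the post-disclosure T0 among the limitations. State that it qualifies conclusions about change from baseline, including the within-arm increase at 3 months.
4. If T0 values are tabulated by arm, present them descriptively and say that they neither confirm nor exclude a reaction to disclosure.
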